## Background

Cardiovascular disease accounts for more deaths than any other disease and ischemic heart diseases, such as acute myocardial infarction (AMI), account for a large proportion of these deaths [1-3]. Timely recognition and reperfusion are life saving interventions [3-7]. Randomized controlled trials have demonstrated the superiority of prehospital fibrinolysis [8-11]; whereas other interventions such as 12-lead [12-15] and bypass to interventional hospitals [6,16-23] have not been subjected to the same rigorous analysis. Based on associations with improved time to treatment, 12-lead ECG and bypass to an interventional hospital has been implemented in many communities which makes it difficult to conduct a controlled trial. In contrast, many rural and urban communities with small volumes may not have implemented any one of these interventions, as such the standard of care for patients presenting with ST-segment elevation myocardial infarction (STEMI) varies between communities[24]. In 2004, the expert panel of Cardiac Care Network of Ontario report recommended that urgent angioplasty should be adopted as the standard of care[24]. Concurrent with this report the Ontario Health Technology Advisory Committee (OHTAC), upon their review of the literature regarding primary angioplasty for the treatment of STEMI, recommended that "every effort should be made to decrease the access time for patients with AMI from onset to symptoms to administration of fibrinolysis or primary angioplasty"[25,26]. This study is being conducted to evaluate different implementation strategies in place currently that could reduce symptom to intervention time in Ontario[25]. The objective of this paper is to describe the design of a study to compare these strategies against time to treatment and survival outcomes as well as cost effectiveness. We hope that this prospective cohort trial will promote the adoption of the optimal implementation strategy into the healthcare system and may provide the information required to directly change health policy and funding for systematic multidisciplinary care involving local EMS systems. We anticipate that the identification and implementation of the best care strategy may provide consistent and optimal care of patients presenting with STEMI across all communities in Ontario,

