## Methods/Design

### Study Design

PREDICT is a prospective, population-based cohort study of four patient care strategies provided by regional EMS services to patients with chest pain and suspected ischemia.

1. 3-lead PHECG and transported to the nearest receiving ED who were not eligible for bypass based on transport time.

2. 3-lead PHECG and transported to the nearest receiving ED who were eligible for bypass based on transport time, if 12 lead PHECG was possible.

3. 12-lead PHECG and prehospital notification transported to the nearest receiving ED who were not eligible for bypass to a PCI center based on transport time.

4. 12-lead PHECG with prehospital notification and eligible for bypassing the nearest receiving ED with transport to a PCI center.

Bypass eligibility was based on transport distance of patients from their pick-up location to PCI center and the cut-off point was 60 kilometres.

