### Setting

This study is set in regions of Ontario with a population of 3,043,853 served by 14 EMS services, under the medical control of 4 regional Base Hospital programs (Table 1)[27]. These regions represent 25% of the population of Ontario and 9.6% of the population of Canada. This geographic region covers 206,727 km^2 ^with variable population densities from 0.6 to 574 persons per km^2 ^representing rural, suburban, urban, and metropolis areas[27].

**Table 1 T1:** List of regional base hospital programs and emergency medical services participating in PREDICT study

Regional Basehospital Programs	Participating Emergency Medical Services (EMS)
Hamilton Health Sciences Centre for Paramedic Education & Research - Hamilton	County of Brant Ambulance Service Haldimand EMS Hamilton EMS Hamilton-Wentworth Regional Ambulance Service Norfolk EMS Six Nations Ambulance Service

North-East Ontario Regional Base Hospital Program - Sudbury	Algoma EMS Manitoulin-Sudbury EMS Sudbury EMS Sault Ste. Marie EMS Timmins EMS

Northwest Region Base Hospital Program	Superior North EMS

Sunnybrook Osler Centre for Prehospital Care - Toronto	County of Simcoe Paramedic Services, Peel Regional Paramedic Services

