### STEMI Identification with 12-Lead PHECG

• Proportion of STEMI subjects within the target door-to-reperfusion times comparing basic vs. advanced life support paramedics.

• Paramedics and computer software interpretation of the 3-lead and 12-lead PHECG of all STEMI subjects will be compared with a gold standard (defined as consensus between two investigators' independent interpretation blinded to paramedic or software interpretation)

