### Analysis Plan

The primary outcome, and treatment time intervals, will be analyzed with one-way ANOVA and subsequent pair-wise multiple comparison procedures across the four treatment strategies. Different covariates (Table 3) will be analyzed using multiple linear regressions and they will be introduced into the model and evaluated as potential confounders. Variables will be retained if they have had an effect of 5% or greater on the coefficients for door-to-reperfusion time. Survival at 30 days and one year for STEMI patients will be analyzed as a binary outcome (Chi square) and as a survival analysis. Covariates that may affect survival will be analyzed with a Cox PH Regression Model. Adverse event rates will be analyzed with a Chi square analysis or a Fisher's exact test.

**Table 3 T3:** Analysis Plan - List of Covariates

1. Presence of cardiac catheterization lab in the primary destination hospital with the ability to perform 24-7 emergent primary angioplasty;
2. Fully affiliated teaching hospital;
3. Is the ED on Time Consideration (TC) or deferral from ambulances based on workload of acutely ill or injured patients?
4. Is the ED on Consideration (C) or deferral from ambulances based on workload?
5. Weekday;
6. Weekend;
7. Time of day in 8 hour intervals (08:00-16:00, 16:00-24:00, 24:00-08:00);
8. Age (as a continuous variable);
9. Sex;
10. History of MI;
11. History of CABG;
12. History of angioplasty;
13. Location of STEMI (anterior, posterior, inferior);
14. Off load delay (minutes);
15. PCA or PCI or bypass surgery.

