### A Priori Subgroup Analysis

• Rural vs. urban settings and academic vs non academic destination hospitals

• Geographical bias subgroup analysis comparing all non PCI capable sites for distance from PCI site;

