By protocol, the data is collected by trained data guardians in all the sites and since almost all the data guardians are geographically remote from the central research coordinating centre the quality of data may suffer and poise a threat to internal validity. In total there are 10 data guardians abstracting prehospital data and 16 data guardians abstracting inhospital data. To encourage uniformity in data collection and to provide oversight and ensure quality, a number of interventions are planned. All data guardians will be individually trained by one of the investigators (VR). The web based data entry system has built in data definitions and abstraction instructions which are accessible through point and click technology on the variable name at the time of data entry. The abstraction instructions are listed hierarchically ensuring that the data is abstracted from the best source if at all possible. All variables are subject to error and logic checks across other variables and across forms (inhospital and prehospital) which are applied at the time of completion and the case will not close without reconciliation of all the error. Web conferences are conducted for all data guardians to highlight changes to the data set structure, upgrades to the software and discuss difficult variables identified by the data guardians or by the investigators. Data reports to test uniformity are planned and will be discussed at weekly team meetings of the research staff and investigator steering meetings.

Technological advances may outpace the study. Some regions/counties that provide 3-lead ECG in the prehospital setting are not currently considering the change in technology, while other areas are in the planning or transitional stages. Any change from 3-lead to 12-lead in a participating site will compromise recruitment rates and regional comparisons. If this happens an additional 3-lead site with similar geographic and demographic characteristics will be recruited and retrospective data collection will occur to permit concurrent comparisons. In anticipation of this threat to the protocol we have engaged each of the EMS medical directors in the decision to participate. The window of the trial has been confirmed to correspond to the planned changes in the services considering a change.

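### Strategy follows region, yet rural/urban setting is only a subgroup and not a Table 3 confounder; paramedic level is also absent and would matter if crew mix differs between strategy groups

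*Protocol article*

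**What the plan says.** Under Study Design the protocol article states: "PREDICT is a prospective, population-based cohort study of four patient care strategies provided by regional EMS services to patients with chest pain and suspected ischemia". ECG capability is a regional property. The Discussion notes: "Some regions/counties that provide 3-lead ECG in the prehospital setting are not currently considering the change in technology".

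On setting, the Background says that "many rural and urban communities with small volumes may not have implemented any one of these interventions". The Setting section gives population densities from 0.6 to 574 persons per square kilometre, "representing rural, suburban, urban, and metropolis areas".

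On adjustment, the Analysis Plan says: "Different covariates (Table 3) will be analyzed using multiple linear regressions and they will be introduced into the model and evaluated as potential confounders". A variable stays in if it changes the coefficients for door-to-reperfusion time by at least 5%. Table 3 has 15 items.

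The two factors at issue appear elsewhere:

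- A Priori Subgroup Analysis lists "Rural vs. urban settings and academic vs non academic destination hospitals".
- The outcomes under STEMI Identification with 12-Lead PHECG include "Proportion of STEMI subjects within the target door-to-reperfusion times comparing basic vs. advanced life support paramedics".

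**The concern.** When treatment follows region, any other feature of the region that affects the outcome is a candidate confounder. Setting is the obvious one. It is fixed before the ECG is taken, it varies widely across the participating services, and the article's own account suggests that it may go with whether 12-lead ECG and bypass were adopted. If 3-lead groups hold more rural or low-volume patients than 12-lead groups, part of any difference in the within-target proportion may belong to the setting. The authors mean the results to inform policy and funding, so the attribution matters.

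Paramedic level raises a similar but weaker question. The article treats it as worth comparing on the primary endpoint, yet leaves it out of the adjustment list.

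**Working it through.** **1. Table 3 against the rest of the article.** The 15 items cover the destination hospital (items 1 and 2), ED workload (3 and 4), weekday, weekend and time of day (5 to 7), age and sex (8 and 9), cardiac history (10 to 12), STEMI location (13), offload delay (14) and procedure (15).

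| Factor | Used elsewhere | In Table 3 |
|---|---|---|
| Academic hospital | Subgroup | Yes (item 2) |
| Rural/urban setting | Subgroup | No |
| Paramedic level | Outcome comparison | No |

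Academic status is thus used both as a subgroup and as a confounder; rural/urban setting is used only as a subgroup.

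**2. Is each factor linked to strategy in the article?**

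- *Setting:* partly. Strategy follows region, regions differ greatly in density, and low-volume communities may have neither intervention. The Background names both rural and urban low-volume communities, so the link is suggested and not measured.
- *Paramedic level:* no. Nothing says how basic and advanced crews are spread across services or strategy groups.

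**3. What controls geography already?**

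- Groups 1 and 3 (not bypass-eligible) and groups 2 and 4 (eligible) compare 3-lead with 12-lead within a distance stratum, because "Bypass eligibility was based on transport distance of patients from their pick-up location to PCI center and the cut-off point was 60 kilometres". This does not separate rural from urban pick-ups inside a stratum.
- Items 1 and 2 describe the destination hospital, not the pick-up setting. Item 1 is also partly determined by bypass, so it is not a clean baseline proxy.

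**4. Scale.** The plan's only relevant figures are in Table 2. With the pooled-variance formula for two proportions (two-sided 0.05, 80% power),

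n = [1.96·√(2p̄q̄) + 0.842·√(p₁q₁ + p₂q₂)]² / (p₂ − p₁)²,

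and the continuity correction n′ = (n/4)·[1 + √(1 + 4/(n·|p₂ − p₁|))]², a 37.4% baseline gives 402, 185 and 107 per arm for differences of 10, 15 and 20 points. Table 2 prints 402, 185 and 106, so it reproduces to rounding. The planned 100 per group is therefore close to the 20-point row.

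**5. Illustration, on assumed inputs.** The article gives neither the effect of setting or crew on the endpoint nor any imbalance. For an omitted factor acting additively,

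bias = (effect on the within-target proportion) × (difference in its prevalence between groups).

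With no true strategy effect, a 37.4% baseline, 100 per group and a two-sided 0.05 pairwise test:

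| Assumed effect | Assumed imbalance | Bias | False-positive rate |
|---|---|---|---|
| 10 points | 20 points | 0.10 × 0.20 = 2 points | 6% |
| 10 points | 40 points | 0.10 × 0.40 = 4 points | 9% |
| 15 points | 40 points | 0.15 × 0.40 = 6 points | 14% |
| 15 points | 60 points | 0.15 × 0.60 = 9 points | 25% |
| 20 points | 80 points | 0.20 × 0.80 = 16 points | 62% |

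A milder assumption, a 5-point effect with a 20-point imbalance, gives 1 point. If there is no imbalance, the bias is zero.

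**The case against.** The case on the other side has real content.

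- **Geography is not ignored.** Besides the 60 km split and items 1 and 2, the plan has a rural/urban subgroup analysis and a geographical-bias subgroup by distance from the PCI site, and any replacement 3-lead site must resemble the one lost in geography and demography. All of this stands as partial control. Strategy contrasts within rural and within urban strata would be informative, but the article does not say that they are combined into an adjusted overall contrast. The replacement rule covers replacement sites only.
- **The endpoint clock starts at the hospital door.** Scene and transport times are separate secondary intervals, so crew skill and rural distance have less room to act. This weakens the mechanism, most of all for crew level. It does not remove it for setting, which can also act through what happens after arrival.
- **The list may not be closed.** The article does not forbid other covariates, and a fuller plan may exist. That is fair. The point rests on what the printed list contains, given what the same article analyses elsewhere.

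A reader might also infer three stronger things that the article does not support. The first is that crew level is an established confounder; no section says that it differs between services or strategy groups. The second is that the basic-versus-advanced comparison is unadjusted and so picks up the 12-lead effect. The article names that comparison without a method, and its heading allows the reading that it concerns 12-lead patients only. The third is a definite size of bias; every figure depends on assumed inputs.

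**Conclusion.** The point holds for setting. Strategy is allocated by region, setting varies widely and may track adoption, and the printed confounder list omits it, so the adjusted four-group comparison is controlled for geography only in part. For paramedic level it holds conditionally: the omission matters if crew mix differs between strategy groups, and the article is silent on that.

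The size is unknown. The illustrative range of 1 to 16 points shows only that a bias worth noticing beside the 20-point difference the sample size supports is possible under strong imbalance, and that it is trivial under mild imbalance. That both variables will be collected is inferred from the planned analyses that need them, since the data-variable files are not shown.

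**What to change.** - Add rural/urban setting, defined by pick-up location, and paramedic level (basic or advanced) to Table 3.
- Keep setting in the adjusted strategy model regardless of the 5% change rule.
- Tabulate both variables by care group before modelling, to show whether there is enough overlap to separate them from ECG type.
- Report the basic-versus-advanced comparison adjusted for, or stratified by, care group.

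The change is to analysis wording, and the planned analyses already need both variables. It costs two extra model terms. Where setting or crew level tracks ECG type closely, intervals will widen and the effects may not be separable at all; the overlap table would show this, and the report should then say so.

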### Sample Size Calculation

The recruitment goal is to enrol 100 STEMI prospective subjects per group (e.g. as in the WEST trial)[28], for a total of 400 STEMI subjects. The primary estimate is based on a difference in the proportion of patients who received reperfusion (fibrinolysis or PCI) within target door-to-intervention times. We based our calculation using estimates from Canto et al., 2002[29]. In that study there was an increase in the percentage of the patients who received lytic therapy within 30 minutes, from 31% to 50% (an absolute difference of 19%). The percentage of patients who received PCI within 90 minutes increased from 29% to 48% (an absolute difference of 19%). Furthermore there was a combined 24% higher odds of receiving fibrinolytic therapy or PCI with the active EMS involvement (odds ratio 1.24, 95% CI 1.21 to 1.28, p < 0.001). Calculations were conducted using PASS software, assuming an alpha (α) of 0.05 and power of 80% (Table 2).

**Table 2 T2:** Sample size calculation for the PREDICT study

Baseline %	Intervention %	Absolute Difference	Odds Ratio	Number per arm
37.4	47.4	10%	1.5	402

37.4	52.4	15%	1.8	185

37.4	57.4	20%	2.3	106

To estimate the number of potential subjects that could be enrolled in the study, the annual rate of STEMIs that would occur within a 60 minute transport time of the closest PCI centre was determined. The surrounding areas within 60 minutes of a PCI centre were first identified using data from a Cardiac Care Network of Ontario (CCN) report published in 2004[6]. Current population estimates were then assigned to each of the surrounding areas using population estimates for 2006[27]. For counties or regions where a proportion of the population resided outside a 60 minute radius, population data from the 2006 Canadian census was used from the census subdivisions to adjust the 2006 population estimates[27]. To determine the rate of STEMI, an estimate of 571 per 1,000,000 inhabitants was calculated by taking an estimate obtained using CIHI data of 6524 STEMIs in Ontario for fiscal 2001/02 and dividing it by the 2006 Ontario Census Population and determining the rate per million inhabitants[6,27]. The number of potential subjects to be entered in per year was then estimated by assuming a 50% transport by EMS rate and a potential recruitment rate of 70%.

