### Ethical Considerations and Human Subjects Protection

PREDICT is an observational, prospective non-interventional study based on review of routinely collected source data and as such meets the requirements for minimal risk research[38-40]. Approval by 47 research ethics boards/committees covering 71 hospitals will be sought to launch the study.

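### ECG type is set by EMS service or region (14 services), but the named tests treat patients as independent, so contrasts that cross ECG type have standard errors that are too small

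*Protocol article*

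**What the plan says.** Study Design describes "four patient care strategies provided by regional EMS services to patients with chest pain and suspected ischemia". Each strategy pairs an ECG type with a bypass status. Bypass eligibility is decided by the distance from the patient's pick-up point to the PCI centre, with a 60 km cut-off, so it varies between patients of one service.

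ECG type is handled differently. The Discussion says "Some regions/counties that provide 3-lead ECG in the prehospital setting are not currently considering the change in technology". It treats a move from 3-lead to 12-lead as an event at a participating site, to be met by recruiting another 3-lead site. Setting describes a population "served by 14 EMS services, under the medical control of 4 regional Base Hospital programs". Ethical Considerations adds the destination level: "Approval by 47 research ethics boards/committees covering 71 hospitals will be sought".

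The Analysis Plan gives one-way ANOVA with pairwise comparisons for the primary outcome and the time intervals. For adjustment it says "Different covariates (Table 3) will be analyzed using multiple linear regressions". Survival is analysed by chi-square, a survival analysis and a Cox model. No random effect, GEE, frailty or cluster-robust variance is named. Sample Size Calculation aims to "enrol 100 STEMI prospective subjects per group" and tabulates numbers per arm in Table 2, with no design effect.

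**The concern.** Patients of one service share dispatch, crews, destination hospitals and catheterization-laboratory processes. These plausibly drive door-to-reperfusion time, so outcomes within a service are likely to be correlated.

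Where the exposure is also set at service level, this correlation does not cancel from the comparison. A 3-lead versus 12-lead contrast then carries information from 14 services rather than from 400 independent patients. ANOVA, ordinary regression, chi-square and standard Cox variances ignore this and return intervals that are too narrow.

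The study is meant to support adoption of the best strategy across communities and to inform budgets. A difference among a few services could be reported as a strategy effect with more certainty than the data carry.

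**Working it through.** **Inputs from the protocol article.** 14 services; 100 STEMI patients per strategy, 400 in total; alpha 0.05, power 80%; baseline 37.4%; Table 2 numbers per arm of 402, 185 and 106 for differences of 10, 15 and 20 points (last row: "37.4 57.4 20% 2.3 106").

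**Assumptions (not in the documents).** ICC of 0.01, 0.02 and 0.05; equal service sizes; seven services per ECG type; each service's patients split evenly by eligibility.

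**1. Table 2 reproduced.** The formula is the pooled two-proportion one, two-sided: n = [1.96·√(2p̄(1−p̄)) + 0.842·√(p1(1−p1)+p2(1−p2))]² / d². With continuity correction, n' = (n/4)·[1+√(1+4/(n·d))]².

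| p1 to p2 | n | n' | Table 2 |
|---|---|---|---|
| 37.4% to 47.4% | 382.2 | 401.9 | 402 |
| 37.4% to 52.4% | 171.4 | 184.5 | 185 |
| 37.4% to 57.4% | 96.7 | 106.4 | 106 |

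The table is therefore an independent-patient calculation.

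**2. Which contrasts cross ECG type.** Strategies 1 and 2 are 3-lead; 3 and 4 are 12-lead. Of six pairs, 1–3, 1–4, 2–3 and 2–4 cross ECG type; 1–2 and 3–4 do not.

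**3. Pooled 3-lead versus 12-lead.** Patients per service m = 400/14 = 28.6. Design effect DE = 1+(m−1)·ICC. True type I error of a nominal 5% test = 2·[1−Φ(1.96/√DE)].

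| ICC | DE | True SE / naive SE | Type I error |
|---|---|---|---|
| 0.01 | 1.28 | 1.13 | 8% |
| 0.02 | 1.55 | 1.25 | 12% |
| 0.05 | 2.38 | 1.54 | 20% |

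**4. One cross-ECG pair.** Seven services supply each 100-patient group, so m = 100/7 = 14.3. The number per arm for 20 points is 106·DE, rounded up. Power uses the uncorrected formula at 100/DE per arm; without clustering it is 81%.

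| ICC | DE | Effective size (100/DE) | Type I error | Number per arm, 20 points | Power, 20 points |
|---|---|---|---|---|---|
| 0.01 | 1.13 | 88 | 7% | 121 | 76% |
| 0.02 | 1.27 | 79 | 8% | 135 | 72% |
| 0.05 | 1.66 | 60 | 13% | 177 | 60% |

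**5. Four-group ANOVA, by simulation.** Beta-binomial outcomes were generated with no strategy effect (rate 37.4%), 14 services and 400 patients, 3,000 runs per setting. ECG type was set by service, and eligibility was mixed at random within ECG type.

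| ICC | ANOVA | Pooled 3- v 12-lead | Pooled eligible v not eligible |
|---|---|---|---|
| 0.01 | 6% | 8% | 5% |
| 0.02 | 9% | 12% | 5% |
| 0.05 | 15% | 21% | 5% |

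The pooled ECG column agrees with step 3. The eligibility column stays near nominal because service effects fall on both sides of that comparison.

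**The case against.** The strongest objection concerns scope. A reader might infer that whole strategies are fixed by service, so that every planned test is inflated. Study Design does not support this: eligibility follows pick-up distance, and one service can supply two strategies. If strategies were wholly nested in services, the simulated ANOVA would run at 11%, 17% and 37%, but that is not the design described. Nor do effective group sizes of 78, 64 and 42 (100 divided by the design effects in step 3) apply to a strategy group, because they place all 28.6 patients of a service in one strategy. This objection stands and limits the point to the contrasts listed.

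Second, Table 3 already includes a 24-7 catheterization laboratory, teaching status, ED deferral and off-load delay, and subgroups by setting and distance are planned. These may lower the residual ICC in adjusted models. They do not absorb the remaining variation between services, and the unadjusted ANOVA and chi-square tests do not use them.

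Third, this is a condensed article, and a fuller analysis plan could attach robust variances to the linear and Cox models. That is fair for those models. It does not rescue the one-way ANOVA positively named for the primary outcome, or the chi-square test, both of which assume independence as written.

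Finally, neither the ICC nor the division of services across strategies is given. The size is therefore illustrative; the direction is not in doubt for any ICC above zero.

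**Conclusion.** The point holds for the four-group test and the four pairwise contrasts that cross ECG type: followed as written, the plan understates standard errors and exceeds its nominal 5%. For 1 versus 2 and 3 versus 4, inflation arises only to the extent that distance to a PCI centre clusters by service.

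At an ICC of 0.01 the excess for the four-group test is small; at 0.05 its error rate is about three times nominal. These figures rest on the assumed ICCs, equal service sizes and an even eligibility split. Unequal services, plausible with densities from 0.6 to 574 persons per km², would usually make matters worse. A reader might take the 8%, 12% and 20% as the error of the main comparison, but they belong to the pooled two-group ECG contrast; the main comparison is the four-group test.

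**What to change.** - **Primary outcome:** replace the ANOVA with a logistic mixed model for the binary outcome, with a random intercept for EMS service, and for destination hospital where estimable. Alternatively, use GEE or cluster-robust standard errors by service with a small-sample correction for 14 clusters. Take the four-group test and pairwise contrasts from that model.
- **Time intervals and survival:** use the same clustering for the time intervals, and a frailty term or robust variance for Cox.
- **Sample size:** state that Table 2 assumes independent patients, and report power or the detectable difference over a range of ICCs.

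The cost is mainly wording and programming. Cases are found from ambulance call reports and completed from receiving-hospital charts, so service and hospital should be identifiable, although the variable lists are in additional files not shown here. The price is wider intervals and a less favourable stated power. The change does not remove confounding between service and ECG type, which the report should state separately.

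### Pick-up distance forms the groups but is not among the Table 3 confounders, so the 3 v 1 and 4 v 2 contrasts are left open to regional differences in geography

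*Protocol article*

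**What the plan says.** Study Design describes an observational comparison: "PREDICT is a prospective, population-based cohort study of four patient care strategies provided by regional EMS services to patients with chest pain and suspected ischemia". The groups cross ECG type with bypass eligibility. Group 1 is "3-lead PHECG and transported to the nearest receiving ED who were not eligible for bypass based on transport time"; group 3 is its 12-lead counterpart. Group 4 is "12-lead PHECG with prehospital notification and eligible for bypassing the nearest receiving ED with transport to a PCI center"; group 2 is its 3-lead counterpart, eligible by location but taken to the nearest ED. The eligibility rule is: "Bypass eligibility was based on transport distance of patients from their pick-up location to PCI center and the cut-off point was 60 kilometres".

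ECG type belongs to the area and not to the patient. The Discussion says: "Some regions/counties that provide 3-lead ECG in the prehospital setting are not currently considering the change in technology". The Setting section describes 206,727 square kilometres with "variable population densities from 0.6 to 574 persons per km" (per square kilometre).

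For confounding, the Analysis Plan states: "Different covariates (Table 3) will be analyzed using multiple linear regressions and they will be introduced into the model and evaluated as potential confounders". A listed covariate stays in if it moves the door-to-reperfusion coefficients by at least 5%. Distance returns only under A Priori Subgroup Analysis: "Geographical bias subgroup analysis comparing all non PCI capable sites for distance from PCI site". Rural v urban setting is also a subgroup only.

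**The concern.** A yes/no cut at 60 km puts patients on one side of a line; it does not balance distance on that side. Groups 2 and 4 may lie anywhere from 0 to 60 km. Groups 1 and 3 start at 60 km with no stated upper limit. Because ECG type is set regionally, 3 v 1 and 4 v 2 compare different regions, and nothing makes their distance distributions alike.

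Pick-up distance is fixed before any strategy acts, so it is a proper candidate confounder. The 5% rule cannot bring it in, because the rule screens only what Table 3 lists. If distance differs between regions and affects the outcome, part of that difference will be read as an effect of 12-lead ECG or of bypass, in a study meant to inform policy and funding.

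**Working it through.** **1. What each contrast holds fixed** (Study Design)

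| Contrast | Side of 60 km | Distance range | First destination |
|---|---|---|---|
| 3 v 1 | beyond | 60 km upward, no stated limit | nearest ED in both groups |
| 4 v 2 | within | 0 to 60 km | PCI centre (4), nearest ED (2) |

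**2. Table 3, item by item.** Items 1 and 2 describe the hospital (24-7 catheterization lab, teaching status). Items 3, 4 and 14 concern ED load and off-load delay, items 5 to 7 the calendar and clock, and items 8 to 13 and 15 the patient, infarct and procedure. None is geographic.

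**3. Which distance reaches which outcome** (Treatment Time Intervals, Primary Outcome)

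- Transport interval: in groups 1 to 3 it depends on distance to the nearest ED. In group 4 the journey to the PCI centre is part of the strategy itself.
- PCI-transfer interval and symptom onset to reperfusion: distance to the PCI centre matters for patients who need PCI.
- Primary outcome (90 min for PCI, 30 min for fibrinolysis): the clock starts at the door, so distance acts only indirectly, through inter-hospital transfer and the choice of reperfusion method.

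**4. The plan's yardstick.** The protocol gives no figure for distance, so Table 2 serves as the scale. For 37.4% v 57.4%, two-sided 5%, 80% power:

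n = [1.960·√(2 × 0.474 × 0.526) + 0.842·√(0.374 × 0.626 + 0.574 × 0.426)]² / 0.20² = 96.7

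With continuity correction: (96.7/4) × [1 + √(1 + 4/(96.7 × 0.20))]² = 106.4, against the stated 106. The other rows reproduce as 402 and 185. The plan therefore looks for differences of 10 to 20 points.

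**5. How imbalance becomes a difference.** With no strategy effect, split one side of the cut into nearer and farther patients:

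spurious difference = (gap in share of nearer patients) × (gap in on-time rate)

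The protocol gives neither gap. Assumed values run from 0.20 × 0.10 = 2 points to 0.60 × 0.30 = 18 points. A middle case is 0.40 × 0.20 = 8 points. With 100 per group, the chance of p < 0.05 is 6%, 74% and 21% respectively.

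**6. A model tied to kilometres.** All inputs are assumed: 80 km/h; half of both groups transferred and timed from the first door; median door-in-door-out time 45 min (log-SD 0.3 to 0.6); 25 min at the PCI site; 40% of lysed patients on target; distance SD 12 km; no strategy effect.

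- Time for a transferred patient = door-in-door-out + (km/80 × 60) + 25. At the median the 90 min target is met up to (90 − 45 − 25) × 80/60 = 26.7 km, so distance matters inside 60 km.
- Inside 60 km, a gap of 10 to 15 km in mean distance gives about 5 to 13 points. With an average rate near 40% and 100 per group, SE = √(2 × 0.4 × 0.6/100) = 0.069. The chance of p < 0.05 is then about 11% at 5 points and 47% at 13 points.
- At 60 km the median time is already 45 + 45 + 25 = 115 min. Almost no transferred patient meets 90 min, so the same model gives at most about 1 point and about 5% rejection.

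**The case against.** The strongest reply concerns mechanism. A reader might infer that a 10 km gap (10/80 × 60 = 7.5 min) feeds straight into every interval, which with an SD of 15 min and 100 per group would make a false positive almost certain (94%). The documents do not support this. In groups 1 to 3 the transport interval ends at the nearest ED, so distance to the PCI centre does not set it; in group 4 the longer journey is a consequence of bypass.

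A reader might also infer that the primary comparison is biased by 5 to 13 points. That does not follow either. The figure needs half of both groups to be transferred, whereas a bypassed group 4 patient arrives directly at the PCI centre. It also needs timing from the first door, and the Primary Outcome section does not say which door counts. Beyond 60 km the model yields almost nothing; what remains for 3 v 1 is a possible route through choice of lysis, which was not modelled.

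Third, the plan handles geography in part. Items 1 and 2 of Table 3 capture something of the hospital route, subgroups by distance and rural/urban setting are planned, and the article is condensed. This lessens the point without removing it. Table 3 is an itemised list, not a summary. In 3 v 1, item 1 should be nearly constant, since these patients live beyond 60 km and go to the nearest ED. In 4 v 2, bypass itself determines item 1, so adjusting for it removes part of the effect under study. The distance subgroup classifies non-PCI hospitals and adjusts no strategy comparison.

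Finally, the protocol does not say that a continuous distance is stored, only that eligibility rested on it. This stands and is dealt with in the change proposed.

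**Conclusion.** The omission is real: as written, the plan uses distance to form the groups and leaves it, with transport time and rural/urban setting, out of the adjustment set for 3 v 1 and 4 v 2. Whether this produces material bias is unknown, because the protocol gives no distance distribution by region, transfer share or on-time rate by distance. The 5 to 13 points illustrate what could happen inside 60 km under a transfer pattern that suits group 2 better than group 4. For 3 v 1 the modelled effect on the primary outcome is close to nil. The exposure is more direct for the secondary time intervals, provided the distance relevant to each is used. This is a weakness that should be corrected; it does not show that the comparison will mislead.

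**What to change.** Add two continuous covariates to Table 3, both fixed before the strategy acts: distance from pick-up to the nearest PCI centre, and distance from pick-up to the nearest receiving ED. Keep both in the adjusted 3 v 1 and 4 v 2 comparisons whatever the 5% rule says, with a non-linear term. Make these comparisons only within each side of 60 km, since groups on opposite sides share no distance range and adjustment across the line would be extrapolation. Restrict 3 v 1 to distances at which both groups have patients.

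The protocol also needs to reconcile how eligibility is described before the covariate is defined: groups 1 to 3 refer to transport time, the cut-off is in kilometres, and the Sample Size section works with 60 minutes.

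The cost is one further derived variable, retention of distance as a continuous value, a few degrees of freedom, and the loss of a few very remote patients from 3 v 1. No patient's care changes.
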